## Background

A high prevalence of polypharmacy, defined as the concurrent use of five or more drugs, is observed among older adults [1]. Although sometimes necessary to treat multiple conditions, polypharmacy has many drawbacks, the most important being an increased risk of drug-related problems, and is a heavy burden for both the patient and the healthcare system [2]. In addition, polypharmacy increases the probability of the use of potentially inappropriate medications (PIMs) [2]. Older adults living in long-term care facilities (LTCFs) are at risk of polypharmacy and PIM use. One study reported that 70% of LTCF residents received five or more prescribed medications [3], and another study reported that approximately 40% of LTCF residents received PIMs compared to 20–25% of older adults living in the community [4]. In South Korea, the average number of medications taken by residents in an LTCF was reportedly 10.6 ± 4.2, those taking ≥ 11 constituted 45.7% [5], and PIM users were reported at 40.7% [6].

Recently, deprescribing, the process of tapering or stopping drugs supervised by a multidisciplinary healthcare professional aimed at minimizing polypharmacy and improving patient outcomes, has emerged as a useful way to reduce both polypharmacy and PIM use [7, 8]. However, research conducted in LTCF residents is still scarce. Furthermore, no systematic approaches to practice are routinely embedded in clinical care to reduce polypharmacy and PIM use among LTCF residents [9].

In this study, we propose testing a multidisciplinary medication management program (MMMP) for LTCF residents, an intervention designed to be suitable for routine use in LTCF settings. We hypothesized that deprescribing via the MMMP would decrease drug-related problems, including the number of medications and PIMs, and improve health-related outcomes.

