### Experimental and control interventions

Each participant included in the study will be randomized into one of the following two groups:

Control group

The control group will receive the typical clinical care, as routinely provided in the LTCFs where the study will take place. The only restriction applied would be that no other planned CMR, deprescribing, or MCC will be performed in the LTCF setting during this phase.

Intervention group

We developed an MMMP for LTCF residents as a multifaceted intervention that integrates available evidence tools and a team approach within a clinical pathway where decision-making is led by considering participants’ priorities.

The research team including physicians, pharmacists, and nurses will be informed of the approach and program development so the intervention is as “fit for purpose” and as feasible as possible [9]. To foster fidelity, participating visiting physicians, pharmacists, and nurses in LTCF will receive an in-person training session for the program and the entire intervention, as well as a demonstrative manual [9].

This program will be operationalized as a structured clinical pathway in an electronic web-based platform, called “MMMP in LTCF” (pacen-mmmpin.com [PACEN; website.ne.kr]). It serves as a shared record for all visiting physicians, pharmacists, and other relevant workforces participating in the pathway for access and review. It is designed to be used in conjunction with and complement the EMR. This platform records and integrates five domains (Supplementary Text 1).

Operational steps (Fig. 3)STEP 1: Explanation of the study and obtaining informed consentSTEP 2: Recruitment and registration of participantsSTEP 3: Collection of participant’s informationSTEP 4: Listing medications taken by the participantSTEP 5: CMR and counseling by pharmacistsSTEP 6: Visiting physicians’ referral for medication reconciliationSTEP 7: Medication reconciliation after the prescribing physician confirms the CMR results.STEP 8: Conducting MCC through the cooperation of multidisciplinary teams (visiting physicians, pharmacists, nurses, and NH workers)STEP 9: Sharing CMR results, deprescribing, and participant managementSTEP 10: Nursing care and monitoring of ADEs by nursesSTEP 11: Medication management education for the multidisciplinary teams in the LTCF.

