#### Clinical evaluation indices

##### Primary endpoints

The primary endpoints are (1) ADEs, (2) the number of PIMs and PIM users, (3) the ratio of PIMs and PIM users, (4) the number and ratio of users of two or more central nervous system (CNS) drugs, (5) all-cause delirium, (6) emergency department visits, (7) admissions, and (8) falls at T1-T6.

An ADE is defined as a severe adverse event, i.e., emergency room visits, hospitalizations, falls, and deaths due to “possible” abnormalities according to the World Health Organization-Uppsala Monitoring Centre causality evaluation criteria [10], or adverse drug reactions (ADRs) due to the use of drugs to be wary of or high-risk drugs for older adults. Medication-related information will be recorded to identify and describe the processes of medication change during and after the intervention. Locally acting topical agents without substantial systemic absorption or effects are excluded from the study. Acute short-course medications, such as antibiotics, are also excluded from the counts. This will be ascertained by a pharmacist after medication reconciliation, using dispensing, EMR, and participant information.

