#### Process evaluation indices

The participants in the intervention arm of the study will be evaluated. In each cluster of LTCF, the number of CMR cases, requests for medication reconciliation (delivery of CMR results to visiting and external physicians), responses to medication reconciliation, ADE monitoring (medication use-related, such as medication management and ADRs), case management cases, the time spent on CMR and MCC, as well as the experience of guardians, visiting physicians, and nurses in the entire cluster are evaluated at the end of the intervention.

Experience evaluation will provide a full picture of their experience with the intervention and the process of describing it at the initial stages of the intervention, as well as at the end. The guardians of participants, visiting physicians, and nurses in the LTCF will also be asked about their satisfaction with the intervention process and with their care around medications using Likert-type scales, as well as free text responses of the strengths and weaknesses of the process, and whether they would recommend the intervention to a family member or friend.

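### The non-severe limb of the ADE primary endpoint counts only reactions to taking drugs, so non-severe harm from stopping them enters no endpoint and the ADE comparison tilts toward the deprescribing arm

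*Protocol article*

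**What the plan says.** Primary endpoints (protocol article) defines an ADE by two alternatives. The severe limb opens with "An ADE is defined as a severe adverse event, i.e., emergency room visits, hospitalizations, falls, and deaths due to" and continues with causality rated as possible on the WHO-UMC criteria. The other limb is "adverse drug reactions (ADRs) due to the use of drugs to be wary of or high-risk drugs for older adults". Neither mentions tapering, withdrawal, rebound or relapse.

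The same section lists all-cause delirium, emergency department visits, admissions and falls as further primary endpoints, with no restriction to drug causes. It also says: "Medication-related information will be recorded to identify and describe the processes of medication change during and after the intervention".

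The Background describes the core of the intervention as "deprescribing, the process of tapering or stopping drugs supervised by a multidisciplinary healthcare professional". For controls, Experimental and control interventions states that "no other planned CMR, deprescribing, or MCC will be performed in the LTCF setting during this phase".

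Process evaluation indices lists "ADE monitoring (medication use-related, such as medication management and ADRs" among its counts, in a section that begins "The participants in the intervention arm of the study will be evaluated".

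**The concern.** A trial of stopping drugs can do harm in two ways: residents may react to drugs they still take, or they may suffer from drugs being reduced or withdrawn. The intervention is meant to lower the first kind and may raise the second. For non-severe events, the ADE definition counts the first kind only.

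The result could be a reported fall in ADEs that partly reflects which events were eligible to be counted. This matters because the Discussion expects a successful result to pass directly into routine care, where a lower ADE rate would be read as evidence that drug-related harm went down overall.

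**Working it through.** The document states no ADE rate, so there is no figure to reproduce. The check is to follow each kind of event through the definitions and then work out the direction.

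**Step 1. Where each event is counted**

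| Event | Attributed to taking a drug | Attributed to stopping or reducing a drug |
|---|---|---|
| Emergency visit, admission, fall | ADE (severe limb) if rated possible; also its own primary endpoint | ADE status not stated; counted in its own primary endpoint |
| Death | ADE (severe limb) if rated possible; also collected | ADE status not stated; collected (Follow-up and data collection) |
| Delirium without a severe event | ADE if a reaction to one of the drug classes named; also its own primary endpoint | Not an ADE as worded; counted in the delirium endpoint |
| Any other non-severe event | ADE if a reaction to one of the drug classes named | Not an ADE as worded; in no other endpoint |

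The last row is the gap. A non-severe reaction to taking a high-risk drug counts, while an equally non-severe reaction to stopping the same drug does not. The first two rows show an ambiguity rather than an exclusion.

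**Step 2. Exposure by arm**

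Deprescribing is part of the intervention, and controls may have no other planned deprescribing. Ordinary stopping under usual care is not barred, so stopping harm in controls need not be zero. Planned stopping, however, occurs in one arm only.

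**Step 3. Direction**

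For each arm let a be the rate of counted ADEs per resident and w the rate of stopping harm left out of the ADE count (I = intervention, C = control).

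- Recorded difference: a_I − a_C
- Full difference: (a_I + w_I) − (a_C + w_C)
- Recorded minus full: −(w_I − w_C)

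The recorded difference therefore flatters the intervention whenever w_I > w_C.

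On the ratio scale, a_I/a_C is below (a_I + w_I)/(a_C + w_C) exactly when a_C × w_I > a_I × w_C. This holds whenever w_I > w_C and a_I ≤ a_C, which is the situation the trial expects.

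**Step 4. Size**

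Suppose total harm were equal in both arms, stopping harm in controls were nil, and a share s of the intervention arm's harm were uncounted. The recorded ratio would then be 1 − s. Any figure would simply restate the assumed s, for which the document gives no value.

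**The case against.** The strongest reply is that the trial does not ignore harm from stopping. The severe limb has no use restriction, so a fall or admission after a drug is stopped could be rated possible and counted. Emergency visits, admissions, falls and all-cause delirium are primary endpoints in their own right, and deaths are collected. Safety and monitoring has any adverse symptom noted at a data collection point passed to the visiting physician and pharmacist. All of this stands. A reader might infer that the ADE endpoint counts only harm from using drugs, or that the trial leaves its main harm unmeasured; the text does not support either. These provisions still do not repair the ADE comparison for non-severe events, because symptoms passed to clinicians feed no endpoint.

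A reader might also infer from the process indices that ADE monitoring is confined to use-related events. That list contains activity counts for the intervention arm, and its parenthesis gives examples. It does not set how the endpoint is ascertained.

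The article is condensed, and Supplementary Text 2, which details the operational steps including ADE monitoring by nurses, is not at hand. It may tell nurses to look for withdrawal effects. The endpoint definition, however, is fixed in the article and would still decide what counts.

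Finally, ADE is one of eight listed primary endpoints, and the sample size rests on PIM users. That limits the weight of the point but does not remove it.

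**Conclusion.** The point holds for non-severe harm other than delirium. As worded, such harm from dose reduction or withdrawal enters no endpoint, and the ADE comparison leans toward the intervention. For severe harm the fault is only that the ADE definition does not say whether events attributed to stopping count; the events themselves are largely captured elsewhere.

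The direction rests on two assumptions: that uncounted stopping harm is more frequent where stopping is planned, and that the definition offers two alternatives, so that a reaction need not be severe to count. If reactions also had to be severe, non-severe events of both kinds would drop out of the ADE count, and the asymmetry would lie only in how severe events are attributed.

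The size cannot be computed. A reader might try to derive it from the sample-size inputs: 40.7% with an odds ratio of 0.41 gives odds of 0.6863 × 0.41 = 0.2814, hence 22.0%, and (0.4070 − 0.2196) × 836 is about 157 fewer PIM users. That is a difference in user status, not a count of drugs stopped. On the 715 per group needed before the dropout allowance it is about 134. Turning either number into uncounted events needs rates that the document does not contain, and would wrongly include severe events already captured.

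**What to change.** Reword the definition so that both limbs cover events due to the use, dose reduction or withdrawal of a drug. State that this applies identically in both arms at every time point, including to drugs stopped under usual care in controls. Report use-related and withdrawal-related events separately as well as combined, so that the present use-based result stays visible.

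A fixed attribution window after each stop is not proposed. The document offers no basis for its length, and such windows would open mostly in the unblinded intervention arm.

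Cost: one more classification item on the ADE record. Medication changes are already to be recorded, although the article does not say that their dates are. Recruitment began in April 2022, so this is a mid-trial clarification of a primary endpoint and should be documented as such. Only the statistician is blinded, so attribution to stopping will be made with knowledge of allocation; the separate reporting is there partly for that reason. The ADE result may look less favourable to the intervention.

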##### Secondary endpoints

Secondary endpoints are the number of medications taken and the number and rate of polypharmacy.

#### Process evaluation indices

The participants in the intervention arm of the study will be evaluated. In each cluster of LTCF, the number of CMR cases, requests for medication reconciliation (delivery of CMR results to visiting and external physicians), responses to medication reconciliation, ADE monitoring (medication use-related, such as medication management and ADRs), case management cases, the time spent on CMR and MCC, as well as the experience of guardians, visiting physicians, and nurses in the entire cluster are evaluated at the end of the intervention.

Experience evaluation will provide a full picture of their experience with the intervention and the process of describing it at the initial stages of the intervention, as well as at the end. The guardians of participants, visiting physicians, and nurses in the LTCF will also be asked about their satisfaction with the intervention process and with their care around medications using Likert-type scales, as well as free text responses of the strengths and weaknesses of the process, and whether they would recommend the intervention to a family member or friend.

### Follow-up and data collection

The evaluation will be performed at six different time points: T1–T6. The study procedure and data collection are detailed in Fig. 1 and have been established as per the SPIRIT guidelines. A research assistant will collect data from the pharmacists in the intervention group. For the control group, they will visit the LTCF and obtain baseline data from the institutional documents or EMR about the participant’s characteristics, including age, sex, general condition (long-term care level, disability, behavioral status [whether bedridden], and bedsores, if any), medical history (comorbidity), family history, vital signs, and laboratory test results. In addition, medication history, medication reconciliation, and outcomes are recorded as part of the clinical intervention. Data for security outcomes (falls, hospitalization, emergency department visits, and death) will be collected from the records or EMR directly from participating LTCFs. In the case of hospitalization or death of a participant during the follow-up period, no questionnaire for subsequent outcomes will be filled.

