### Education for pharmacists and nurses in the long-term care facilities

The pharmacist will perform the CMR for the participants, who will be educated on the methodology of performing CMR before the study by attending a course organized by researchers at the college of pharmacy. A separate education session will be organized in each LTCF for nurses and workers, presenting the conduct and documents of the study and introducing them to the platform.

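### Data collection is described by arm and the two relevant sections conflict, so equal ascertainment of the medication and adverse drug event endpoints is not assured

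*Protocol article*

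**What the plan says.** All references are to the protocol article.

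- **Follow-up and data collection, intervention arm:** "A research assistant will collect data from the pharmacists in the intervention group".
- **Same section, control arm:** "For the control group, they will visit the LTCF and obtain baseline data from the institutional documents or EMR about the participant’s characteristics". The list that follows covers demographics, care level and general condition, medical and family history, vital signs and laboratory results. It names no medication or ADE outcome.
- **Same section, next sentence:** "medication history, medication reconciliation, and outcomes are recorded as part of the clinical intervention".
- **Same section, falls, hospitalization, emergency visits and death:** these "will be collected from the records or EMR directly from participating LTCFs", with no distinction by arm.
- **Primary endpoints, medication information:** "This will be ascertained by a pharmacist after medication reconciliation, using dispensing, EMR, and participant information". No arm is named.
- **Education section:** "The pharmacist will perform the CMR for the participants". The source in the intervention arm is therefore also the provider.
- **Experimental and control interventions:** reconciliation is Step 7 of the intervention pathway and follows the review of Step 5. Nurse monitoring for ADEs is Step 10. For controls the only restriction is that "no other planned CMR, deprescribing, or MCC will be performed in the LTCF setting during this phase".
- **Blinding:** facilities and researchers know the allocation; only the analysing statistician does not.

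**The concern.** An arm comparison is interpretable only if the outcome is found in the same way in both arms. Here the written route for the intervention arm runs through the staff who deliver the programme, and no matching route at follow-up is written for controls. If a pharmacist working through a full review compiles one arm's drug list and someone reading a chart compiles the other's, the difference in PIM users mixes the effect of deprescribing with the effect of how carefully the list was made.

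The endpoints exposed are important ones. The number of PIM users is the endpoint on which the trial was sized. PIM counts, use of two or more CNS drugs and ADEs are all listed as primary, and medication count is secondary. The ADE definition adds a judgement: an event counts if a drug is a possible cause under the WHO-UMC criteria, or if it is a reaction to a high-risk drug. Both depend on who looks and how hard.

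The Discussion's answer to detection bias is to follow a pre-determined method. That does not help if the method itself is not the same in both arms. A blinded statistician cannot undo a difference that arises at collection.

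**Working it through.** **Step 1. Set the sections side by side.**

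| Item | Intervention arm | Control arm |
|---|---|---|
| Baseline characteristics | From the pharmacists | Facility documents or EMR |
| Medication list, T2 to T6 | From the pharmacists; recorded within the clinical intervention | Not stated in the follow-up section; the primary-endpoint section, if it covers all, says a pharmacist after reconciliation |
| Falls, emergency visits, admissions, death | LTCF records or EMR | LTCF records or EMR |
| ADE causality and reactions without such an event | Source not stated; Step 10 monitoring is present | Source not stated; no counterpart to Step 10 described |

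**Step 2. Try to read the primary-endpoint section as one method for everyone.** It then requires reconciliation in controls. In the pathway, reconciliation follows confirmation of the review results, and planned reviews are barred in controls. Applying it to controls would bring in a part of the intervention; not applying it leaves measurement different by arm. Neither reading agrees with the follow-up section without a change of wording.

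**Step 3. Size of the problem for PIM users.** The protocol gives 40.7% PIM users. It gives no detection rates, so relative shortfalls of 10% and 20% in one arm are assumed as a range, with no true effect.

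- Full detection: odds = 0.407/0.593 = 0.686.
- 10% shortfall: 0.407 × 0.9 = 0.366; odds = 0.366/0.634 = 0.578.
- 20% shortfall: 0.407 × 0.8 = 0.326; odds = 0.326/0.674 = 0.483.

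| Shortfall | In intervention arm | In control arm |
|---|---|---|
| 10% | OR = 0.578/0.686 = 0.84 | OR = 0.686/0.578 = 1.19 |
| 20% | OR = 0.483/0.686 = 0.70 | OR = 0.686/0.483 = 1.42 |

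**Step 4. The same shortfalls if the planned effect is real.** An odds ratio of 0.41 on 40.7% implies odds of 0.686 × 0.41 = 0.281, that is 22.0% in the intervention arm. The observed odds ratio becomes 0.36 (10%) or 0.31 (20%) if the shortfall is in the intervention arm, and 0.49 or 0.58 if it is in the control arm.

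**Step 5. Chance of a spurious result.** The planned size is 715 per group. The article gives no intracluster correlation; 0.05 is assumed, with 65 analysed per cluster (715/11).

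- Design effect = 1 + 64 × 0.05 = 4.2.
- Effective size = 715/4.2 = 170 per group.
- As a check on the assumption: two-sided 5%, 95% power, 40.7% against 22.0% with continuity correction needs 167 per group, and 167 × 4.2 = 702 after rounding up, within 2% of the planned 715.

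With no true effect, the chance of p < 0.05 in the direction of the bias is about 12% for a 10% shortfall and about 34% for a 20% shortfall, against a nominal 2.5% in one direction. No sample-size figure in the protocol changes.

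**The case against.** The strongest reply is that the protocol never says control medication and ADE outcomes come from facility documents or EMR. A reader might infer this, and so conclude that the endpoints are demonstrably measured differently by arm. The text does not support that. The control-arm sentence is limited to baseline characteristics, and the only statement of how medication use is ascertained names a pharmacist, dispensing data, EMR and participant information without naming an arm. It may be meant for everyone. This stands, and the point is therefore a conflict and a lack of assurance, not proven unequal measurement.

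Other tempting extensions also fail:

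- **Nurses as the source of endpoint ADEs.** Step 10 is part of the programme and is not described as endpoint ascertainment. ADE monitoring is listed among the process indices for the intervention arm.
- **Delirium.** No source is given for either arm, so no difference can be claimed.
- **PIM counts biased downward.** Reconciliation may remove stale entries, but it may also uncover drugs prescribed by external physicians. A fall in the count because drugs were really stopped is the treatment effect.
- **A bias that can never be disentangled.** Dispensing records and the national insurance data mentioned in the Discussion could allow a common-source check.

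It is also fair to say that an odds ratio of 0.84 is far from the planned 0.41. The shortfalls assumed here could not by themselves produce the expected effect.

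What the reply does not remove is the explicit sentence that sends intervention-arm data through the pharmacists, and the one that records medication history and outcomes within the clinical intervention. These are stated procedures, not detail left to another document.

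**Conclusion.** The concern holds in a limited form. The follow-up section and the primary-endpoint section conflict, and following them as written does not assure equal ascertainment of the number of PIMs, PIM users, use of two or more CNS drugs, medication counts, reactions not tied to a recorded event, and ADE causality. Falls, emergency visits, admissions and death are outside the point, apart from their attribution to a drug.

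The direction of bias is unknown. For PIM users with no true effect, the apparent odds ratio ranges from 0.70 to 1.42 over assumed relative shortfalls of up to 20% in either arm. That is too small to mimic the planned effect, but enough to turn no effect into an apparent benefit or harm more often than the nominal error rate allows. The detection rates and the intracluster correlation of 0.05 are assumptions; the finding about the text does not depend on them.

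**What to change.** Reconcile the two sections so that one procedure applies to both arms:

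1. At each of T1 to T6 the research assistants extract the medication list from the same records (dispensing and EMR) on the same form in both arms.
2. PIMs and use of two or more CNS drugs are classified from that list by fixed explicit criteria, with the arm label removed.
3. Endpoint ADEs are derived from the same record abstraction in both arms. ADEs found only through Step 10 or the platform are reported as process data, alongside the process indices already listed.
4. Optionally, the national insurance data planned for dropouts are requested for all participants as a common-source check.

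The cost is protocol wording and a common form, using research assistants already in the plan; item 4 adds a wider data request. The downside is that endpoint ADE counts in the intervention arm become less sensitive, because events seen only by the programme's own monitoring no longer count towards the endpoint.

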#### Data analysis

The analysis will follow the intention-to-treat approach.

All analyses will be performed using SAS software (version 9.4; Cary, NC, USA). Statistical significance is defined as *p* < 0.05. This methodology follows the Consolidated Standards of Reporting Trials Statement (http://www.consort-statement.org/consort-statement) [12]. Interim analysis is planned at midpoint after the start of participants’ enrollment and when issues arise during the study, and missing data will not be replaced. If issues arise during the study, the study design will be modified.

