### Loss to follow-up

We anticipated a conservative maximum loss to follow-up rate of 15%. Participants lost to follow-up will be classified as such because they elected to no longer be part of any further follow-up (withdrawal of consent) or were unable to participate because of discharge, hospitalization, death, etc. In the case of discontinuation of research at an LTCF before the completion of the registration of 76 participants, the target of one cluster, participants already registered at the LTCF are included in the study for intervention and follow-up, and the remaining participants are recruited from other similarly-sized LTCFs (number of residents). In cases where participants who are lost to follow-up do not explicitly withdraw consent, medication and healthcare utilization data will still be collected from participant charts via chart audits where possible [9].

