In our study, participants and researchers are not blinded due to the nature of the intervention (open-label study). To minimize the bias caused by this, we implemented cluster study design. Additionally, in order to minimize performance and detection bias, the study will be conducted according to a pre-determined method according to the protocol. Moreover, if there are indicators with significant differences between the intervention group and the control group when analyzing the results later, they will be adjusted using statistical techniques. Furthermore, in order to minimize attrition bias in the outcome analysis, we will follow the intention-to-treat approach, and data on those who dropped out will be obtained and analyzed from data of the National Health Insurance Sharing Service (It refers to a vast amount of data amounting to 1.3 trillion cases, including demographic information about each patient, details of prescribed drugs, prescribed medical tests and health checkup results, and long-term care insurance data for the elderly, of all citizens).

We developed a multidisciplinary medication management program (comprehensive medication reviews, deprescribing, and multidisciplinary case conferences) to assess its impact on medication use and health problems among LTCF residents. This program, with a high level of evidence as a study with a long-term follow-up period targeting a large population, is immediately scalable, and the results of the trial, if successful, are anticipated to be directly translatable into clinical practice [9] and will become a part of routine preventive care in LTCF residents. Evidence from this study will help to understand the provision of a systematic approach to reducing the burden of polypharmacy and PIMs, as well as providing a systematic clinical pathway for implementation. Based on our results, intervention methods suitable for other settings should be developed.

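### The article ends outcome forms at hospitalisation, itself a primary endpoint, and does not say how a resident who returns is followed; delirium and ADE causality then have no stated recovery route

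*Protocol article*

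**What the plan says.** Under Primary endpoints, the article lists ADEs and PIM use ("The primary endpoints are (1) ADEs, (2) the number of PIMs and PIM users") and continues to "5) all-cause delirium, (6) emergency department visits, (7) admissions, and (8) falls at T1-T6". The same section defines an ADE so that it includes hospitalisations judged at least possibly drug-related under a named causality scale.

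Follow-up and data collection contains two adjacent statements. The first gives a record-based source: "Data for security outcomes (falls, hospitalization, emergency department visits, and death) will be collected from the records or EMR directly from participating LTCFs". The second is a stop rule: "In the case of hospitalization or death of a participant during the follow-up period, no questionnaire for subsequent outcomes will be filled".

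The sample size section counts hospitalisation within the 15% dropout allowance. Loss to follow-up includes participants who "were unable to participate because of discharge, hospitalization, death, etc", and then says that, unless consent is explicitly withdrawn, "medication and healthcare utilization data will still be collected from participant charts via chart audits where possible".

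Data analysis specifies intention-to-treat and adds that "missing data will not be replaced". The Discussion says that, to limit attrition bias, "data on those who dropped out will be obtained and analyzed from data of the National Health Insurance Sharing Service".

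**The concern.** Hospitalisation has two roles here. It is an outcome the programme is meant to influence, and it is an event that ends the outcome form and counts as loss. The stop rule puts it on the same footing as death, although a hospitalised resident may return to the facility and again be observable for every endpoint.

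If the form does stop, the residents still observed at later time points are those not hospitalised. Should hospitalisation differ between arms, these are differently selected groups, and comparisons on the affected endpoints are no longer protected by randomisation. Staff at one facility could follow the stop rule while staff at another follow the chart-audit rule. In an open-label trial randomised by facility, such variation can line up with arm. Data not collected at the time cannot be restored by a later analysis plan.

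**Working it through.** **Endpoint by endpoint: what is stated after a hospitalisation**

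| Primary endpoint | Source that could continue | Covered after hospitalisation? |
|---|---|---|
| Admissions, emergency visits | Facility records or EMR; chart audit of utilisation | Probably; not stated for returners |
| Falls | Facility records or EMR | Probably; not stated for returners |
| PIM use, CNS drugs | Chart audit of medication, where possible; prescribed drugs in insurance data | Partly |
| ADEs | Component events from records | Causality judgement not named in any recovery source |
| Delirium | None named | No stated route |

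The Discussion describes the insurance data as demographics, prescribed drugs, tests and check-ups, and long-term care insurance data. The chart audit covers medication and utilisation. Neither description names delirium or ADE causality. No primary endpoint is described as a separate questionnaire measure, so it is reasonable to read *questionnaire* as the outcome form.

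**The plan's own loss figure.** 1,430/(1 − 0.15) = 1,683, against 1,672 stated (0.7% apart); 22 clusters × 76 = 1,672 exactly. The allowance reproduces, and hospitalisation is inside it.

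**Effect on power.** Inputs from the article: 40.7% PIM users, odds ratio 0.41 (so 22.0% in the intervention arm), 836 per arm, 76 per cluster. The article states no ICC. I assume 0.048, close to the value implied by 715 per arm: 157 per arm are needed without clustering, and (715/157 − 1)/75 = 0.047. With loss *d*, the design effect is 1 + (76(1 − d) − 1) × 0.048 and the effective size per arm is 836(1 − d) divided by it.

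| Loss | Design effect | Effective n per arm | Power |
|---|---|---|---|
| 15% | 4.05 | 175 | 97% |
| 25% | 3.69 | 170 | 96% |
| 35% | 3.32 | 164 | 96% |
| 45% | 2.96 | 155 | 95% |

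A *t* reference with 20 degrees of freedom lowers the level slightly (95.6% to 93.3% over the same range), but the loss remains small.

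**How bias could arise.** The documents give no rate for delirium or ADEs, so I use PIM use, the endpoint with a stated rate, as an illustration. It shows the mechanism and is not a forecast, since PIM data may be partly recovered. Assume no true effect, overall PIM use of 40.7% in both arms, and PIM use *q* among those lost. PIM use among those retained is r = (0.407 − d·q)/(1 − d).

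- Equal loss, 15% in each arm: r is the same in both arms, so the odds ratio is 1.00.
- Loss 30% control, 20% intervention, q = 0.5: r = 0.257/0.70 = 0.367 and 0.307/0.80 = 0.384; odds ratio 1.07. With q = 0.7: 0.281 and 0.334; odds ratio 1.28.
- Loss 35% control, 15% intervention, q = 0.5: 0.357 and 0.391; odds ratio 1.15. With q = 0.7: 0.249 and 0.355; odds ratio 1.66.

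All values of *d* and *q* are assumptions.

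**The case against.** The strongest reply is that the rules can be read in sequence: the form stops, chart audit continues for medication and utilisation, insurance data cover dropouts, and whatever is still missing is not imputed. On that reading nothing is impossible to follow. This largely stands, and it rules out several stronger inferences.

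- A reader might infer that all outcome collection stops at the first hospitalisation. The text stops a questionnaire, the sentence before it takes falls, admissions, emergency visits and death from records, and the word *first* does not appear.
- A reader might infer that repeat admissions are never counted. If that were so, with assumed Poisson rates of 0.3 to 1.0 admissions per resident, 14% to 37% of admissions would be missed and a true rate ratio of 0.70 would appear as 0.73 to 0.80. The record source and the utilisation audit point the other way, so I do not rely on these figures.
- A reader might infer a breach of intention-to-treat. Leaving missing values unimputed does not by itself breach analysis as randomised. It does weaken the Discussion's claim to minimise attrition bias.
- A reader might infer that the 15% allowance will be exceeded. Over five three-month intervals it corresponds to 1 − 0.85^(1/5) = 3.2% per interval, if every exit is permanent. No hospitalisation rate is given to compare with this.

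Choosing a mixed model, imputation or a competing-event method is analysis-plan material and is no part of this point. What the objection does not answer is the resident who returns, or delirium and ADE causality after a hospitalisation. Those depend on collection rules that the article itself states.

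**Conclusion.** The point holds as an unreconciled conflict over follow-up after hospitalisation. A primary-endpoint event is also listed as a reason for loss, and the article does not say which rule applies to a resident who returns. The gap is clearest for delirium and ADE causality. For PIM use and utilisation it is partial, because recovery is planned where possible.

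The size of the bias cannot be given. It depends on hospitalisation rates, on whether they differ by arm, and on how those lost differ from those retained. With equal loss in similar residents the illustration shows none. Power is little affected: about 97% falling to 95% as loss rises from 15% to 45%, under an assumed ICC of 0.048. This should be fixed, but it does not by itself invalidate the trial.

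**What to change.** Reconcile the sections on follow-up and data collection, sample size, data analysis and loss to follow-up with the Discussion, endpoint by endpoint:

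1. State that hospitalisation is an outcome and not a reason to end data collection.
2. For residents who return, collect all primary endpoints, including delirium, ADEs and PIM use, again at the next scheduled time point.
3. End collection only at death or withdrawal of consent.
4. Remove hospitalisation in itself from the loss-to-follow-up definition, and align the dropout wording in the sample size section.
5. Apply the planned chart audit and insurance data in the same way in both arms.
6. Handle death separately from missing data, and say that the rule on not replacing missing data applies to what remains after these steps.

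The cost is protocol wording and modest additional abstraction from sources the trial already plans to use. No extra participants are needed and clinical care is unchanged.
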